### **2.3 Data Sources**

Potentially eligible patients will be identified using Duke Electronic Health Record (EHR) data, with additional inclusion and exclusion criteria (See protocol section 3.2). No additional data will be used to implement the analyses. Recruitment messages were sent to eligible patients between September 2019 and March 2022.

Invitations to participate in the study will be distributed until the primary study's target sample size meets the requirements set in the protocol (See protocol section 3.1). A REDCap database will be created with the relevant recruitment information and assigned factorial arm. If a participant engages with the invitation's Mytonomy link the responses will be recorded by Mytonomy and delivered to the team in a .csv file upon completion of the study. The consenting information and survey comprehension in the Mytonomy file will be used as endpoints.

### 3. Analysis Population and Missing Data

#### 3.1 Study Phenotypes

The population will be identified using Duke EHR and will consist of a subset of patients contacted to participate in the primary study. All inclusion and exclusion factors for the primary study are applicable to the current analyses (See protocol section 3.2).

The current study's recruitment criteria will consist of adult patients who receive care in the Duke Health System, and who fall into 1 of 4 risk group phenotypes:

- #1: Patients with obesity (BMI  $\geq 30$ ) and high 10-year ASCVD risk ( $\geq 20\%$ )
- #2: Patients with obesity (BMI  $\geq 30$ ) and low 10-year ASCVD risk ( $< 7.5\%$ )
- #3: Patients with normal weight (BMI 18-25) and low 10-year ASCVD risk ( $< 7.5\%$ )
- #4: Patients with normal weight (BMI 18-25) and high 10-year ASCVD risk ( $\geq 20\%$ )

#### 3.2 ASCVD Risk Score Calculation

ASCVD risk over 10 years will be determined using the Pooled Cohorts Equation. For blood pressure and cholesterol (Total Cholesterol & HDL) measures, we will calculate the empirical 1% and 99% quantiles. Any measures more extreme than these values will be truncated to the 1% and 99% respectively. For those missing any measurements (smoking, cholesterol, etc.), the worst and best case scenarios (based on the 1% and 99%) will be imputed. If a participant's ASCVD risk score is still low risk under the worst case scenario or high risk under the best case scenario, they will be categorized as such. Otherwise they will be excluded from randomization.

For the calculation of ASCVD risk score, we will determine if a participant had been or was currently on an anti-hypertensive medication from January 1, 2019 and onward.

#### 3.3 Mid Study Review

A scheduled mid study review was conducted. Per the protocol in section 8.2 if one consenting strategy appeared weaker than the other the less effective strategy will be discontinued. The mid-study review did not indicate that any consenting method had a worse response rate. Therefore, no change was made to the study and all methods will be included in the analysis.

#### 3.4 Multiplicity Adjustments

Multiplicity will be controlled at  $\alpha=0.05$  for the statistical tests associated with the primary objective. A single interim analysis of the primary endpoint was conducted at  $\alpha=0.01$ , leaving the remaining  $\alpha=0.04$  for the final analysis. A global 3 df hypothesis test of any difference between the four consenting strategies will be tested at  $\alpha=0.04$ , and confidence intervals for effect estimates for the primary endpoint (relative risks) will be reported with nominal 96% confidence. Multiplicity will not be controlled between the primary and secondary endpoint analyses, and the secondary endpoint will be tested at  $\alpha=0.05$ , and effect estimates reported with nominal 95% confidence intervals. Subgroup analyses for the primary

endpoint will be considered exploratory, with interactions tested at nominal  $\alpha=0.05$ . All other estimates will be reported with nominal 95% confidence limits.

### 3.5 Missing Data

No imputation will be performed; missing data will be excluded from all denominators.

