## 5. Sub Groups of Interest

All covariates were collected through Duke EHR at the time the recruitment invitation was sent.

#1: Age – Less than or greater than or equal to 60 years' old

#2: Sex – Male or Female

#3: Race – White, Black or African American or Other

#4: Study Phenotype - as defined in Section 3.1 of SAP.

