| Male                                    | 567 (36.9%)                               | 147 (38.1%)                                         | 152 (39.7%)                                   | 131 (33.9%)                                        | 137 (36.1%)                  |
| Race                             |                                           |                                                     |                                               |                                                    |                              |
| White                                   | 1,130 (73.6%)                             | 278 (72.0%)                                         | 277 (72.3%)                                   | 277 (71.8%)                                        | 298 (78.4%)                  |
| Black or African American               | 309 (20.1%)                               | 79 (20.5%)                                          | 82 (21.4%)                                    | 84 (21.8%)                                         | 64 (16.8%)                   |
| Other                                   | 70 (4.6%)                                 | 19 (4.9%)                                           | 18 (4.7%)                                     | 20 (5.2%)                                          | 13 (3.4%)                    |
| Not Reported/Declined                   | 26 (1.7%)                                 | 10 (2.6%)                                           | 6 (1.6%)                                      | 5 (1.3%)                                           | 5 (1.3%)                     |
| BMI                              |                                           |                                                     |                                               |                                                    |                              |
| Median (25th, 75th)                     | 31.8 (23.8, 36.4)                         | 32.2 (23.7, 36.8)                                   | 31.8 (23.6, 36.2)                             | 31.7 (23.9, 36.2)                                  | 31.9 (24.2, 36.4)            |
| Min, Max                                | 18.1, 5042                                | 18.4, 5042                                          | 18.4, 76.5                                    | 18.6, 66.7                                         | 18.1, 52.1                   |

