| White                   | 1.01 ( 0.88, 1.16)                                       | 0.88 ( 0.76, 1.02)                                     | 0.94 ( 0.82, 1.08)                                      |                                   |
| Black                   | 1.36 ( 1.04, 1.78)                                       | 1.15 ( 0.86, 1.53)                                     | 1.28 ( 0.97, 1.68)                                      |                                   |
| Other                   | 0.98 ( 0.65, 1.5)                                        | 0.63 ( 0.35, 1.11)                                     | 0.78 ( 0.47, 1.28)                                      |                                   |
| Gender           |                                                          |                                                        |                                                         | 0.67                              |
| Male                    | 1.12 ( 0.93, 1.36)                                       | 0.95 ( 0.77, 1.17)                                     | 1.1 ( 0.9, 1.34)                                        |                                   |
| Female                  | 1.05 ( 0.9, 1.21)                                        | 0.89 ( 0.76, 1.05)                                     | 0.94 ( 0.81, 1.09)                                      |                                   |
| Study Phenotypes |                                                          |                                                        |                                                         | 0.2                               |
| Obese High Risk         | 1.14 ( 0.94, 1.39)                                       | 0.92 ( 0.74, 1.14)                                     | 1.07 ( 0.88, 1.31)                                      |                                   |
| Obese Low Risk          | 1.13 ( 0.75, 1.71)                                       | 0.94 ( 0.76, 1.15)                                     | 1.08 ( 0.9, 1.29)                                       |                                   |
| Non-obese Low Risk      | 0.98 ( 0.7, 1.38)                                        | 0.81 ( 0.57, 1.16)                                     | 0.83 ( 0.58, 1.2)                                       |                                   |

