**Table 6. Robust log linear Poisson regression for the association of the exposure group, sub groups and the interaction (exposure group x subgroups) of on having a comprehension of consent form score  $\geq 5$ . Population = patients who completed consent.**

|                         | Text and Physician Video vs. Text Only
RR (95% CI) | Text and Patient Video vs. Text Only
RR (95% CI) | Text and Animated Video vs. Text Only
RR (95% CI) | Global Interaction p-value |
|-------------------------|-------------------------------------------------------|-----------------------------------------------------|------------------------------------------------------|----------------------------|
| Age (Years)      |                                                       |                                                     |                                                      | 0.66                       |
| ≤60                     | 0.96 ( 0.88, 1.05)                                    | 0.97 ( 0.89, 1.07)                                  | 0.95 ( 0.87, 1.05)                                   |                            |
| <60                     | 1.05 ( 0.94, 1.17)                                    | 1.04 ( 0.92, 1.17)                                  | 0.98 ( 0.87, 1.12)                                   |                            |
| Race             |                                                       |                                                     |                                                      | 0.37                       |
| White                   | 1 ( 0.93, 1.08)                                       | 1 ( 0.93, 1.08)                                     | 0.99 ( 0.91, 1.07)                                   |                            |
| Black                   | 1.12 ( 0.9, 1.39)                                     | 1.05 ( 0.83, 1.32)                                  | 1.03 ( 0.82, 1.3)                                    |                            |
| Other                   | 0.75 ( 0.53, 1.06)                                    | 0.98 ( 0.75, 1.28)                                  | 0.67 ( 0.42, 1.07)                                   |                            |
| Gender           |                                                       |                                                     |                                                      | 0.33                       |

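### The 'Other' race row of Table 4 silently includes the 26 people whose race was not reported or declined, and Table 6 uses the same coding

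*Combined protocol and SAP*

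**What the plan says.** SAP section 5 lists race as a subgroup of interest with the levels "White, Black or African American or Other". It does not define 'Other' further and has no level for unknown race. SAP section 3.5 states the missing-data rule: "No imputation will be performed; missing data will be excluded from all denominators". SAP section 4 adds that the number missing will be shown for categorical variables.

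Table 1 of the Appendix has four race lines. 'Other' is 70 people (physician 19, patient 18, animated 20, text only 13). "Not Reported/Declined" is a separate line of 26 (10, 6, 5, 5 in the same order). The race percentages use all 1,535 as denominator.

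Tables 4 and 6 have three race lines: White, Black and Other. Neither a footnote nor the text says how the 26 were handled. SAP section 3.4 calls the subgroup analyses of the primary endpoint exploratory.

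**The concern.** Table 1 separates 'Other' from people of unknown race, so a reader will take the 'Other' row of Table 4 to be those same 70 people. If the 26 were folded in, one label covers two different groups in one set of tables. The 'Other' risk ratios and the race interaction p-values then describe a grouping that SAP 5 does not spell out. The mix also differs by arm, so the comparisons within the row are not between equally composed groups.

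The race rows will be read, because protocol section 4.2 gives low enrolment of non-white patients as part of the case for video consent.

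**Working it through.** **Inputs.** Arms are in the order physician, patient, animated, text only.
- Table 1 group sizes: White 278, 277, 277, 298; Black 79, 82, 84, 64; Other 19, 18, 20, 13; Not Reported/Declined 10, 6, 5, 5.
- Table 4 'Other' row against text only: 0.98 (0.65, 1.5); 0.63 (0.35, 1.11); 0.78 (0.47, 1.28). Race interaction p = 0.3.
- Table 2a consents: 241, 203, 223, 221.
- Table 6 'Other' row: 0.75 (0.53, 1.06); 0.98 (0.75, 1.28); 0.67 (0.42, 1.07). Race interaction p = 0.37.
- Table 5: scores of 5 or more over quiz-takers are 207/238, 177/203, 187/222, 193/221.

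**Formula.** For a/n consenting in a video arm and b/m in text only, RR = (a/n)/(b/m). With arm, subgroup and their interaction in the model, the robust Poisson 95% interval is exp(ln RR ± 1.96 × √(1/a − 1/n + 1/b − 1/m)). All integer counts were searched for agreement with every printed RR and limit to two decimals.

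**Table 4, 'Other' as in Table 1 (19, 18, 20, 13).** There is no solution. The closest counts miss at least one printed figure by about 0.05.

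**Table 4, 'Other' plus any number of the 26 in each arm.** Exactly one combination fits: all 26 added (29, 24, 25, 18), with one set of counts.

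| Arm | Consented/N | RR against 12/18 | 95% CI |
|---|---|---|---|
| Physician | 19/29 | 0.983 | 0.646 to 1.496 |
| Patient | 10/24 | 0.625 | 0.352 to 1.111 |
| Animated | 13/25 | 0.780 | 0.474 to 1.284 |

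**Cross-check on arm totals.** Black has one solution: 57/79, 50/82, 57/84, 34/64. White has three; the one that meets the arm totals is 165/278, 143/277, 153/277, 175/298. Then:
- physician 165 + 57 + 19 = 241
- patient 143 + 50 + 10 = 203
- animated 153 + 57 + 13 = 223
- text only 175 + 34 + 12 = 221

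These are the Table 2a totals, so all 1,535 people are in the race analysis. A generalised score test of the interaction on these counts gives p = 0.299, against the printed 0.3 (a Wald test gives 0.36).

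**Share of unknown race in the Table 4 row.** 26/96 = 27%: physician 10/29 = 34%, patient 6/24 = 25%, animated 5/25 = 20%, text only 5/18 = 28%.

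**Table 6.** Over all denominators up to the pooled consent counts 19, 10, 13, 12, the only fit is 13/19, 9/10, 8/13, 11/12. This gives 0.746 (0.526, 1.059), 0.982 (0.751, 1.283) and 0.671 (0.423, 1.066). The denominators equal the pooled Table 4 consent counts, so the coding is the same. The row has 19 + 10 + 13 + 12 = 54 people. With White 146/163, 128/143, 134/152, 156/175 and Black 48/56, 40/50, 45/57, 26/34, the arms sum to the Table 5 figures and the score p is 0.375 (printed 0.37).

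**Table 4 with the 26 removed.** The documents do not give consents among the 26, so this can only be bounded.
- Assumption: the 26 consented at their arm's pooled rate. 'Other' becomes 12/19, 8/18, 10/20, 9/13. The RRs are 0.91 (0.55, 1.50), 0.64 (0.34, 1.21) and 0.72 (0.41, 1.28). The interaction p is about 0.35 (score) or 0.39 (Wald), N = 1,535 − 26 = 1,509.
- Random allocation of consents within arm: the RRs fall mostly within 0.75 to 1.28, 0.43 to 0.83 and 0.59 to 1.02. The score p falls mostly within 0.07 to 0.52. The Wald p is below 0.05 in about 0.6% of allocations.
- Logical limits: text only has 7 to 12 consents among 13, and the video arms have 9 to 19 of 19, 4 to 10 of 18 and 8 to 13 of 20. The RR limits are 0.51 to 1.86, 0.24 to 1.03 and 0.43 to 1.21.

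**The case against.** The strongest reply is that no rule was broken. The documents nowhere say that "Not Reported/Declined" is missing data. Table 1 gives it a named line with percentages, whereas blood pressure and cholesterol have explicit 'Missing' lines. Table 1 also drops missing values from a categorical denominator elsewhere. Treated for hypertension prints 48.8%, 46.3% and 52.8% for counts of 188, 177 and 200. Those match 188/385, 177/382 and 200/379, not the full arms (48.7%, 46.2%, 52.6%). On that reading a declined answer is a recorded response, and a residual third level is a natural reading of SAP 5.

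Much of this stands. A reader might infer a plain breach of SAP 3.5, but that follows only if the category is taken as missing. For the same reason, Table 1's race percentages on 1,535 are not an established error. What the reply does not remove is the inconsistency: 'Other' means 70 people in Table 1 and 96 in Table 4, SAP 5 does not say that unknown race belongs there, and nothing discloses the merge.

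A reader might also carry the 26 people and the 27% over to Table 6. The documents do not support that. Table 6 covers only consenters with a quiz score, and the number of its 54 'Other' people who are of unknown race is not given.

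It is also fair that the effect on any conclusion is small. All three printed 'Other' intervals in Table 4 already include 1.

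**Conclusion.** The point holds as a minor reporting and coding defect. In Table 4, all 26 people of unknown race were analysed as 'Other', making up 27% of that row and between 20% and 34% by arm. Table 6 uses the same pooled coding, with an unknown share. This rests on the robust Poisson variance formula and on rounding to two decimals. Support comes from the single solution for the row, the exact arm totals and the matching interaction p-values. The White counts are a weaker check, because they were chosen from three fits by the arm totals.

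A reader might go further and infer that the race findings would change. The documents do not show this. The primary result and the White and Black rows are unaffected, the analyses are exploratory, and a significant interaction after exclusion is unlikely, although the most extreme allocations cannot rule it out. The 'Other' estimates without the 26 can be obtained only from the sponsor's data.

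**What to change.** Re-run the race rows and the race interaction tests of Tables 4 and 6 with the Not Reported/Declined people excluded. For Table 4 this means N = 1,509 with 'Other' at 19, 18, 20 and 13. For Table 6 it means the quiz-takers of known race. Alternatively, show these people as a separate level.

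State in SAP 5 which handling applies, and make Table 1 agree. If they are treated as missing, Table 1 should report 26 missing and base race percentages on 1,509 (White 1,130/1,509 = 74.9% instead of 73.6%). If they are a category, the current Table 1 can stay and Tables 4 and 6 should show that category.

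The cost is one re-run of two subgroup tables. The drawback is a smaller 'Other' row with wider intervals.

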## 4. General Methodology

Medians, 25th and 75th percentiles, minimum, maximum and number of missings will be presented for continuous variables; the number and percentage of patients in each category will be presented for categorical variables as well as the number of missings. Analyses will be performed using validated SAS software (SAS V 9.4, SAS Institute, Inc, Cary, NC) and R V 4.0.2. Appropriate statistical models will be used to examine the effect of consenting method on signing the Mytonomy consent form which will be used for both the primary and secondary outcomes in the study.

## 5. Sub Groups of Interest

All covariates were collected through Duke EHR at the time the recruitment invitation was sent.

#1: Age – Less than or greater than or equal to 60 years' old

#2: Sex – Male or Female

#3: Race – White, Black or African American or Other

#4: Study Phenotype - as defined in Section 3.1 of SAP.

## 6. Descriptive Analyses of Patient Inclusion and Characteristics

We will enumerate the number of patients participating in this study (including phenotype #4), the numbers randomized to each exposure group, and the numbers included in the final analysis. Participants are excluded from the final analysis for the following reasons:

- Patients incorrectly consented
- Patients consented more than once

Patient Characteristics: Year of invitation, Risk group phenotypes (groups 1-4) as determined by above risk group criteria from EHR, Age, Gender, Race, BMI, Systolic Blood Pressure (mm Hg), Diastolic Blood Pressure (mm Hg), Total Cholesterol (mg/dL), HDL Cholesterol (mg/dL), Diabetic status, Smoker and Treated for hypertension.

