### **2.2 Randomization**

Once participants click on the 'click to consent' on the 'landing page' the individuals will be assigned the consenting strategy using simple 1:1:1:1 randomization to one of four consent methods (See protocol section 4.2.2).

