## 7. Primary Endpoint

Electronic consenting on the Mytonomy website is recorded as Consent, Declined, or Not Consent. For the primary endpoints the endpoint will be dichotomized as yes (Consent) vs. no (Declined or Not Consent).

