## 9. Primary Endpoint Analyses

### 9.1 – Primary Endpoint: Descriptive Summaries

Endpoint Description: Electronically consenting on the Mytonomy website dichotomized as yes vs. no.

Additional Stratification Factors: None

Statistical Tests:

The total number of consented participants and the total number of participants who landed on the Mytonomy website will be reported for all intervention groups using a binomial distribution with a normal approximation (i.e., Wald confidence limits) the proportion and 95% CI for consenting on the Mytonomy website will be reported.

Report:

Risk group and exposure groups will be enumerated and the proportion and 95% CI for landing will be reported. For patients who consented, the time from landing to consent will be summarized with descriptive statistics. [Tables 2a](#), [Table 2b](#)

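### SAP section 6 removes randomised people for reasons that arise only through consenting, so the primary analysis set depends on the primary endpoint; direction and size cannot be known from the text

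*Combined protocol and SAP*

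**What the plan says.** **Randomisation.** SAP section 2.2: "Once participants click on the 'click to consent' on the 'landing page' the individuals will be assigned the consenting strategy using simple 1:1:1:1 randomization". Assignment therefore comes before any consent decision.

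**Endpoint.** SAP section 7: "the endpoint will be dichotomized as yes (Consent) vs. no (Declined or Not Consent").

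**Exclusions.** SAP section 6 undertakes to give "the numbers randomized to each exposure group, and the numbers included in the final analysis", so the two counts may differ. It then states: "Participants are excluded from the final analysis for the following reasons". The two reasons are "Patients incorrectly consented" and "Patients consented more than once".

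**What the text does not supply.** Incorrect consent is not defined. No rule keeps a repeat consenter once, in the first assigned arm. No analysis set of all randomised people is named, and no sensitivity analysis puts the excluded people back. SAP section 3.5 ("No imputation will be performed; missing data will be excluded from all denominators") concerns missing values, whereas the people dropped under section 6 have a recorded consent action.

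**Denominator wording.** SAP section 9.1 says "the total number of participants who landed on the Mytonomy website will be reported", although landing on the site precedes randomisation.

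**The concern.** A randomised comparison is protected only while the analysed set is fixed independently of what happened after assignment. Here both reasons for removal need an act of consent, which is the endpoint itself. A person who declined or never completed the form cannot meet either. The assigned format could also influence whether someone signs twice or signs wrongly, so removal need not be equal across arms.

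What is at stake is the consent proportion in each arm (Table 2a), the relative risks and global test (Table 3), and the subgroup relative risks (Table 4). The reported global p of 0.07 lies near its 0.04 threshold, so the composition of the analysed set deserves a check.

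**Working it through.** **Inputs.** Table 2a, consented/total: physician video 241/386, patient video 203/383, animated video 223/386, text only 221/380; overall 888/1,535. Final alpha 0.04 and 96% intervals (SAP sections 3.4 and 9.2). I take these counts to be the set left after the section 6 exclusions.

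**Step 1: reproduce the plan's figures.** For each arm, l = ln(y/n) and v = 1/y − 1/n. This is the large-sample equivalent of a robust Poisson model with arm as the only term.

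| Arm | y/n | l | v |
|---|---|---|---|
| Physician | 0.624 | −0.4710 | 0.001559 |
| Patient | 0.530 | −0.6348 | 0.002315 |
| Animated | 0.578 | −0.5487 | 0.001894 |
| Text only | 0.582 | −0.5420 | 0.001893 |

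The 96% interval for a relative risk is RR × exp(±2.054 × √(v₁ + v₀)). For physician video, √(0.001559 + 0.001893) = 0.0588, giving 1.074 (0.952, 1.211). Patient video gives 0.911 (0.798, 1.041) and animated 0.993 (0.875, 1.127). All three match Table 3.

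The global test is W = Σ(l − l̄)²/v, with l̄ the inverse-variance mean, −0.5411. The terms are 3.15 (physician), 3.79 (patient), 0.03 (animated) and 0.00 (text only), so W = 6.97 on 3 df and p = 0.073. Table 3 reports 0.07. The arithmetic is right for the set analysed.

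**Step 2: direction of bias.** Suppose m people were dropped from an arm.
- If they should count as 'yes', the full proportion is (y + m)/(n + m), which exceeds y/n: the reported figure is too low.
- If they should count as 'no', it is y/(n + m), which is below y/n: the reported figure is too high.

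A valid repeat consenter falls under the first case. An incorrectly consented person could fall under either, because the term is undefined.

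**Step 3: size under assumed numbers.** The number excluded per arm is not in the supplied text, so every m below is an assumption.

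| People restored | Coded | RR vs text only | Global p |
|---|---|---|---|
| None | – | as Table 3 | 0.073 |
| 10 in every arm | yes | 1.070 / 0.915 / 0.993 | 0.077 |
| 8, physician only (249/394) | yes | 1.087 | 0.039 |
| 8, physician only (241/394) | no | 1.052 | 0.154 |
| 7, patient video only (203/390) | no | 0.895 | 0.038 |
| 10, patient video only (213/393) | yes | 0.932 | 0.137 |
| 8, animated only (231/394) | yes | 1.008 | 0.074 |
| 8, text only (229/388) | yes | 1.058 / 0.898 / 0.979 | 0.070 |

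Three relative risks are in the order physician, patient, animated; a single one is for the arm altered.

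Balanced removal shifts the proportions but hardly the ratios: with 10 'yes' per arm, physician video goes from 0.624 to 0.634 and text only from 0.582 to 0.592.

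**Step 4: non-differential removal.** Restored consenters were allocated at random across arms in proportion to each arm's consenters (20,000 draws). With 8 or 10 restored as 'yes', p fell below 0.04 in under 0.1% of draws; with 20, in under 1%.

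**The case against.** **The count may be trivial.** SAP section 6 commits to enumerating those randomised, those analysed and the exclusions, and the disposition diagram is simply not visible here. The number could be zero, small or balanced. This stands: no actual bias is shown, and the unseen figure is not a fault of the plan.

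**These are data-cleaning steps.** Removing duplicates and invalid records is ordinary. That would answer the point if the same check applied to everyone, but the stated reasons can reach only people who consented. A repeat consenter who may have seen two formats can be handled by first assignment without being deleted. It would go too far, though, to infer that non-consenters with repeat visits or abandoned attempts were kept: no section describes how they were treated.

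**A few exclusions decide the result.** A reader might infer this from the 8-person physician-video scenario. The documents do not support it. That scenario needs all 8 in one arm and all coded 'yes'; coded 'no', the same 8 move p to 0.154. Nothing in the text shows removal differing by arm.

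**The stated hypothesis does not turn on it.** Hypothesis 4a favours the animated video, whose relative risk is 0.99. Restoring 20 consenters to that arm alone gives 1.03 and a global p of 0.065. In the physician arm, the 96% interval against text only excludes 1 only after 32 one-sided restorations. This stands, and it limits the consequence.

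**Changing the analysis set now is data-driven.** Results are tabulated, so replacing the primary analysis after seeing p = 0.07 would raise its own problem. This stands and shapes the fix.

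**Conclusion.** The point holds as a structural defect. On a plain reading of section 6, the final analysis set is selected after randomisation on the primary endpoint, with no first-assignment rule, no definition of incorrect consent and no analysis restoring those removed.

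The size is unknown. Balanced exclusion leaves the relative risks and the global p almost unchanged (0.073 to 0.077 with 10 restored per arm). Exclusion concentrated in one arm could move p in either direction; the scenarios tabulated run from 0.038 to 0.154. These figures rest on assumed counts and on Table 2a being the post-exclusion set.

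A reader might also infer that every arm's consent proportion is too low. That follows only if all excluded people were valid consents. If some incorrectly consented people should be 'no', dropping them pushes the proportion up.

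The use of landing as the denominator in section 9.1 is a matter of wording: the Table 2a totals (386, 383, 386, 380) already equal the arm sizes in Table 1, so no estimate changes.

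**What to change.** 1. Define the analysis set as every person randomised at the click-to-consent step, analysed in the arm first assigned.
2. Count a person who consented more than once as a single 'consented', using the first signature.
3. Define incorrect consent, keep those people in the denominator under one fixed outcome code, and run the alternative code as a sensitivity analysis.
4. Report exclusions by arm and by reason.
5. Because results exist, show the all-randomised analysis beside the current one in Tables 2a, 3 and 4, labelled as a post hoc correction.
6. In SAP section 9.1, describe the denominator as those randomised.

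The cost is a SAP wording change, one re-run and a disclosed change to the analysis set. It presumes that the excluded records were retained, which the documents do not state.
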